## Methods

### Study aims and hypotheses

Our study aims and hypotheses are three-fold: (1) Characterize the variability in trajectories of CIPN symptoms and physical functioning in patients across treatment and 1 year of recovery. We hypothesize that there will be significant congruence between worsening CIPN symptoms and declining physical activity, mobility, and self-reported physical functioning and disability; (2) Identify 2 or more distinct trajectories of change in symptoms and functioning associated with significant differences in fall rates. We hypothesize that we can identify 2 or more distinct trajectories of CIPN and physical functioning associated with falls; and (3) Identify the simplest set of predictors that identify patients at risk for CIPN-related functional decline and falls. We hypothesize that some combination of patient characteristics (e.g., age, sex, comorbidities, body mass index), chemotherapy features (e.g., chemotherapy drug class, number of chemotherapy cycles, cumulative chemotherapy dose), and mobility measures (gait, balance) will predict distinct trajectories of change in CIPN symptoms and physical functioning [9, 19, 20].

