### Descriptive variables and other measures of interest

Demographic variables, medications (including chemotherapy), cancer health history, and body mass index are collected at baseline and updated throughout the study via the EHR and an in-house questionnaire. The presence of chronic health conditions is measured with the Charlson Comorbidity Index [52]. Cumulative chemotherapy doses and relative dose intensities are calculated from the EHR.

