#### Confounding

We will test the influence of and include, as appropriate, all known confounders in our longitudinal and latent class models.

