#### Specific analysis plan

The analysis will proceed in a series of stages.

*Hypothesis 1.1:Worsening neuropathy symptoms will be associated with concomitant worsening in functioning. *

The change over time in each symptom and functioning outcome will be modeled using a mixed-effects modeling framework implemented in the lme4 statistical package for R. The fixed and random effects structure and the shape of change across time (e.g., linear versus nonlinear) will be determined through likelihood ratio model testing and information criteria. Intercepts (initial status) and growth estimates (e.g., linear and/or quadratic trends) will be estimated for each individual patient for each outcome. All pairs of neuropathy symptom and functioning intercepts and slopes will be correlated to test Hypothesis 1.1*.*

*Hypothesis 1.2. At least two classes of patients with distinct trajectories of change in symptoms and functioning can be identified, and will be associated with significant differences in fall rates.*

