 Each patient's intercept and growth estimates for each measure will be entered into a GMM to identify patient clusters with distinct symptom and function trajectory profiles. For each patient, a probability of belonging to each latent class will be assigned, and the highest membership probability will be used to make a final class assignment. Identification of the best-fitting model will be based on information criteria (e.g., Bayesian Information Criterion), where smaller numbers indicate a better fit, convergence (entropy > 0.80), the proportion of the sample in each latent class (not < 5%), posterior probabilities (mean probability of belonging in “most likely” class near 1.0), and the Lo-Mendell-Rubin adjusted likelihood ratio test (which is used to compare alternative models, e.g., k vs. k-1 classes) [53]. After a good fitting GMM model is found, the resulting latent classes will be described with respect to differences between initial CIPN symptom and functioning profile and change across time. Standard statistics (e.g., t-tests) will then be used to compare fall rates between the observed symptom and function latent classes. We will focus interpretation on effect sizes and 95% CIs. Beyond examining fall rates across the study time course, we will also explore survival models to predict time to first fall. Kaplan Meier models, Mantel-Cox log-rank tests and generalized Wilcoxon-Breslow tests will be used to evaluate differences in the distribution of time to first fall. Multivariate hazard ratios with 95% CIs and Wald χ2 statistics will be calculated from Cox models with Schoenfeld residuals used to test proportional hazards assumptions.

*Hypothesis 2.1. Sociodemographic (e.g., age, sex, comorbidities, body mass index), clinical (e.g., type of chemotherapy, # of chemotherapy cycles and/or cumulative dose of chemotherapy, disease stage, other symptoms), and mobility measures (gait and balance) can be used to predict distinct trajectories of change in neuropathy symptoms and functioning.*

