 Standard statistical tests will be used to examine the association between latent class membership and sociodemographic, clinical, and mobility measures depending on level of scale (e.g., Kendall/s tau-b or Kruskal–Wallis tests). Since we will recruit both men and women into the study, we can also address sex as a biologic variable in the context of symptoms, functioning, and falls among cancer survivors**.** Thus, we will be the first to determine if sex associates with specific symptom trajectories that might lead to either gender-specific management approaches or a uniform strategy. Since there is a potentially large number of variables that will be compared we will control for false discovery rates with the Hochberg adjustment [59].

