## Discussion

CIPN is a distressing and disabling side effect of systemic cancer therapy. In addition, severe CIPN during treatment often results in dose reductions or discontinuation of chemotherapy, which may reduce therapeutic efficacy and worsen prognosis. After cancer treatment ends, lingering CIPN continues to negatively impact physical functioning and quality of life in many survivors. The incidence of CIPN is rising because more neurotoxic agents have been developed and are used to treat a wider variety of cancers, multi-drug chemotherapy regimens have become more common, and cancer survivors are living longer [10]. Currently, clinical guidelines for management of CIPN focus on pain relief, leaving clinical practice with little information about in whom, when, and how to intervene to prevent other downstream consequences of CIPN [10]. The present study will address these knowledge gaps by identifying risk profiles associated with CIPN-related mobility impairments, points in care where early intervention might be best timed to prevent disability and falls, and which mobility deficits to target.

To our knowledge, this is the first longitudinal study to simultaneously track objective and patient-reported CIPN, physical functioning, mobility, physical activity, and falls across chemotherapy and into recovery. In addition to performance measures obtained in the clinic setting, we use wearable devices to measure the quantity of activity and quality of mobility in patients’ everyday living environments. Measures of mobility during daily life are more sensitive than clinical tests at detecting impairments leading to fall risk in older adults [45]. In the present study, the use of wearable devices to capture early changes in functional mobility and activity across treatment and recovery may improve the ability to detect impending functional decline and future fall risk, even before decrements are observed with standard tests of gait and balance or patients report mobility problems.

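### Hypothesis 2.1 treats delivered dose, which neuropathy can itself reduce, and gait and balance measures, which probably also form the classes, as predictors of trajectory class

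*Protocol article*

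**What the plan says.** Under Specific analysis plan, Hypothesis 2.1 names candidate predictors of the trajectory classes. They include the number "of chemotherapy cycles and/or cumulative dose of chemotherapy, disease stage, other symptoms), and mobility measures (gait and balance) can be used to predict" those classes. Study aims and hypotheses gives much the same list for the third aim. The method is to "examine the association between latent class membership and sociodemographic, clinical, and mobility measures" with simple tests such as Kendall's tau-b or Kruskal–Wallis, followed by a Hochberg adjustment.

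On dose, Descriptive variables and other measures of interest says: "Cumulative chemotherapy doses and relative dose intensities are calculated from the EHR". The Discussion says that "severe CIPN during treatment often results in dose reductions or discontinuation of chemotherapy".

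On how the classes are built, the first stage is described thus: "The change over time in each symptom and functioning outcome will be modeled". Then each patient's "intercept and growth estimates for each measure will be entered into a GMM", where the intercept is defined as initial status. The first hypothesis counts mobility among the functioning outcomes, since it pairs "worsening CIPN symptoms and declining physical activity, mobility, and self-reported physical functioning and disability". The Physical functioning section contains postural sway, Timed-Up-and-Go and daily gait from the instrumented socks.

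**The concern.** A predictor should come before the outcome and be measured separately from it. Two groups of candidates in Hypothesis 2.1 do not clearly meet that condition.

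**Dose and cycles.** A patient whose neuropathy worsens may have doses reduced or chemotherapy stopped, and so ends with fewer cycles and a lower cumulative dose. Those totals are then partly results of the trajectory they are meant to predict. Dose also causes neuropathy, so the two directions oppose each other in a single association test.

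**Gait and balance.** If a measure's intercept and slope helped to sort patients into classes, a later test of that measure against class asks whether the classes differ on something they were formed to differ on.

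The third aim is a simple, early set of predictors that could enter clinical pathways. A real dose effect could be missed or shown with the wrong sign, and a mobility test could be credited with predictive value that comes only from how the classes were made.

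**Working it through.** **1. The plan's own figures.** The plan has 2 + 6 = 8 measures at 20 patients each, so 8 × 20 = 160 complete cases, and 160 / (1 − 0.20) = 200 to enrol. For d = 0.40, 2(1.960 + 0.842)² / 0.40² = 98.1, so 99 per group and 198 in total. For w = 0.25 with 4 degrees of freedom, the noncentral chi-square gives 191. All reproduce at 200 evaluable. No stated figure is wrong and the point does not depend on them; 160 is used below as the analysed number.

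**2. Direction of the dose association.** The dose variables come from the health record alongside relative dose intensity, with medications updated during the study, so they read as delivered dose. The Discussion supplies the path from neuropathy to dose. Hypothesis 2.1 fixes neither planned dose nor an early cut-off.

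**3. Size, dose.** Assumed: 160 patients; the worst 30% form a class (48 against 112); planned dose normal; dose cut by 15–50% in 35% (or 20%) of the worst class and 5% of the others; Mann–Whitney test, two-sided 0.05. Delivered dose = planned dose × (1 − cut).

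With *no true dose effect*, the share of studies in which lower delivered dose goes significantly with the worse class is as follows (nominal 2.5% in that direction):

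| Planned-dose CV | 35% vs 5% cut | 20% vs 5% cut |
|---|---|---|
| 15% | about 73–76% | about 26–27% |
| 30% | about 46–47% | about 13–15% |
| 40% | about 29–33% | about 10–12% |

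Over CV 10–40% the range is about 10–83%, with the top at the narrowest planned-dose spread. At p < 0.005 (0.05 / 10, to illustrate ten tests), the CV 15% row falls to about 43% and 8%.

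With *a true effect of 0.3 SD per SD of planned dose*, delivered dose shows it in the right direction in about 1% of studies at CV 15% with 35% cut, and in 19% (35% cut) and 47% (20% cut) at CV 40%. Over all scenarios the range is about 1–49%. Planned dose shows it in about 80%.

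A second set-up used 200 patients, two equal classes, planned-dose SD 5% of the mean and 5% cut in the mild class. An excess of 10, 20, 30 or 40 percentage points of patients cut in the severe class gave false significance in 25%, 67%, 97% and 99.8% of runs, with mean tau-b −0.07, −0.14, −0.21 and −0.28. So narrow a planned-dose spread favours the artefact.

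**4. Gait and balance, the text side by side.** Stage 1 models every functioning outcome; stage 2 enters the intercept and growth estimates of each measure; gait and balance sit under functioning; Hypothesis 2.1 tests gait and balance. Using the baseline value does not separate the two sides, because the intercept is initial status and is itself a class input.

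**5. Size, gait and balance.** Assumed: 200 patients, 8 measures × 2 estimates = 16 class inputs, one continuous symptom factor and one function factor, no true classes, no link between the factors, a two-class Gaussian mixture and a Kruskal–Wallis test at 0.05. A mobility intercept that is a class input was significant in 100% of 1,000 runs, at within-block correlation 0.3 and at 0.5. An unrelated variable left out of the mixture was significant in 4.8% and 5.7%. A different set-up (six measures with a shared factor, baseline unrelated to change) gave 70% with intercepts as inputs and 7% with slopes only.

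**The case against.** **Dose is also a cause of neuropathy.** A reader might infer that the analysis must conclude that lower dose goes with worse neuropathy. The documents do not support that. The two directions compete, and the balance depends on how often doses are cut for neuropathy and how widely planned dose varies, neither of which is stated. The study pools taxanes, platinums and vinca alkaloids across cancers, so a wide spread is plausible, and that shrinks the false-positive figures. This limit stands. The loss of a true effect remains in every scenario run.

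**Multiplicity is controlled.** The Hochberg step lowers the false-positive rates, as shown, but it does not remove a bias.

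**The six function measures are not named.** A reader might infer that every gait and balance result is true by construction. The article lists many more functioning measures than six, and says the models will be kept parsimonious after preliminary work. A gait or balance measure left out of the class model is not circular in this sense. This stands, and the overlap is an inference from the text. It is a likely one, since each functioning measure is said to be entered.

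**Adjustment for confounders.** The Confounding section says: "We will test the influence of and include, as appropriate, all known confounders in our longitudinal and latent class models". A reader might infer that age, sex or drug class would be adjusted away and then tested. The section names no covariate and leaves inclusion to judgement, so the text does not establish this.

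**Timing is detail for a fuller plan.** An article need not say which visit's Timed-Up-and-Go is tested, and the stated intent is early prediction. That is fair on timing alone. The point here rests on what the article does state: the named predictors, the class inputs and the test.

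**Conclusion.** The point holds in two limited parts and should be fixed before Hypothesis 2.1 is analysed.

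First, number of cycles and cumulative dose, read as delivered values, are partly consequences of the trajectory. Their association with class can be attenuated, nullified or reversed, and need not be reversed. The ranges in the working (about 10–83% falsely inverse; about 1–49% correct against about 80% for planned dose) rest on assumed cut rates, cut sizes, class size and planned-dose spread, and precede the Hochberg adjustment.

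Second, for any gait or balance measure that is both a class input and a tested predictor, the association is built in, and a baseline value does not cure it. The extent of overlap is inferred, and the 70% and 100% come from invented structures, so they show the mechanism and not its size in this study.

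Neither part touches age, sex, body mass index, comorbidity, disease stage or drug class as candidate predictors.

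**What to change.** For Hypothesis 2.1:

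- Use planned regimen, planned cycles and planned cumulative dose as candidate predictors, or dose received up to a fixed early landmark. Report delivered dose and relative dose intensity by class descriptively.
- Test symptoms and mobility at their baseline value only.
- Do not test as a predictor any gait or balance measure, or other symptom, whose intercept or slope forms the classes. Either leave it out of the class model or report it as a class descriptor. Name the six function measures so that the split is visible.

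Forming the classes from slopes alone would also reduce the overlap, but it discards initial status, which the plan deliberately models, so it is a trade-off and not the preferred remedy.

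The cost is wording in the analysis plan. Relative dose intensity already needs a planned dose, so no new data collection or change in sample size is evident. The downside is that delivered-dose results become descriptive, and some mobility measures serve as either indicator or predictor but not both.

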Once we characterize the variability in symptom and functioning trajectories, we will determine the simplest set of predictors that identify patients at risk for CIPN-associated functional decline and falls. We will consider multiple patient, behavioral, and clinical attributes that may increase predictive capacity for CIPN. Several possible risk factors that increase the likelihood of developing CIPN have been suggested, including comorbidities, age, smoking, obesity, and inactivity [9, 19, 20]. Cross-sectional studies have identified single attributes associated with higher CIPN, but only a longitudinal study can differentiate between causal factors and co-occurring problems to identify which and why patients are at risk for CIPN, associated mobility problems, and/or falls. We will also evaluate whether treatment characteristics (e.g., number of cycles, cumulative dose, etc.) and simple mobility tests (e.g., TUG) that can quickly be performed in a clinic setting improve predictive power.

Determining how, when, and in whom neurotoxic cancer treatment increases the risk of falls and disability will provide a more nuanced and comprehensive understanding of the presentation and progression of treatment-related impairments. Early identification of simple, early predictors of functional decline and developing fall risk would enable providers to closely monitor those patients at greatest risk of developing CIPN that becomes severe enough to limit mobility and increase fall risk. This knowledge would also facilitate shared decision-making between providers and patients regarding balancing clinical outcomes and quality of life during treatment planning. Incorporating simple measures of impending functional decline into clinical pathways would alert providers when symptoms progress enough to warrant interventions such as dose reductions, switching treatments, and/or referral to rehabilitation. Identifying which mobility deficits to target would contribute to an evidence base for preventive and rehabilitative programs that improve function and in turn lower fall and disability risk. Collectively, these practices would mitigate disability and falls associated with cancer treatment and improve quality of life in cancer survivors.

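### The Hypothesis 2.1 analysis tests one variable at a time, so it cannot deliver the smallest predictor set that Aim 3 promises or any measure of prediction

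*Protocol article*

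**What the plan says.** The Abstract and the aims section make a minimal predictor set one of the study's main products. Aim 3 is to "Identify the simplest set of predictors that identify patients at risk for CIPN-related functional decline and falls". Its hypothesis begins "We hypothesize that some combination of patient characteristics" and goes on to list chemotherapy features and mobility measures as well. The Discussion repeats the intention ("we will determine the simplest set of predictors that identify patients at risk for CIPN-associated functional decline and falls") and says the team will also evaluate whether treatment characteristics and "simple mobility tests (e.g., TUG) that can quickly be performed in a clinic setting improve predictive power".

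The analysis for this aim is under Hypothesis 2.1 in the Specific analysis plan: "Standard statistical tests will be used to examine the association between latent class membership and sociodemographic, clinical, and mobility measures", with the test chosen "depending on level of scale (e.g., Kendall/s tau-b or Kruskal–Wallis tests"). The only further rule concerns multiplicity: "Since there is a potentially large number of variables that will be compared we will control for false discovery rates with the Hochberg adjustment".

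Three other places touch on modelling:
- Under Hypothesis 1.2, multivariable Cox models for time to first fall are to be explored.
- The Confounding section says known confounders will be considered in the longitudinal and latent class models.
- The sample size section says parsimonious models will be fitted, in a passage about the growth mixture model.

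**The concern.** A smallest set, a combination and added predictive power are all joint questions. Each asks what a variable contributes once others are known. The named tests, Kendall's tau-b and Kruskal–Wallis, relate one variable to class membership and ignore the rest. A multiplicity adjustment changes how many variables pass but does not make the question joint.

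Followed as written, the aim ends in a list of adjusted p-values. If several mobility tests measure much the same thing, the list may carry several of them where one would do. If effects are weak, it may omit real predictors. Either way it does not say how well any set separates at-risk patients from others, or whether a quick clinic test adds to age and drug class. The Discussion foresees simple measures of impending decline entering clinical pathways, and that use needs both answers.

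**Working it through.** **1. The plan's own figures.** The sample size section gives d = 0.40 and w = 0.25 (up to 4 degrees of freedom) for class comparisons at 80% power, two-sided α 0.05 and two equal groups.
- Continuous: n per group = 2(z₀.₉₇₅ + z₀.₈₀)²/d² = 2 × 7.849/0.16 = 98.1, so 99. With 100 per group the detectable d is 2.802 × √(2/100) = 0.396.
- Categorical, 4 df: the noncentrality for 80% power is 11.935, so N = 11.935/0.25² = 190.96, so 191. Power at N = 200 is 0.820.

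Both reproduce with 200 analysed. Both are for comparing one variable between classes. The section gives no figure for prediction.

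**2. Promise against method.**

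| Promised | What it needs | What Hypothesis 2.1 provides |
|---|---|---|
| Smallest set (Aim 3) | A rule for dropping variables made redundant by others | Separate tests |
| A combination (Aim 3 hypothesis) | A joint model of class | Separate tests |
| Improved predictive power (Discussion) | A performance measure with and without the added tests | None |

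**3. Size, by simulation.** The documents give neither the correlations among mobility measures nor the strength of any predictor, so every input here is an assumption. In all settings, one mobility measure truly predicts class. The other mobility measures correlate with it (common correlation ρ) but have no effect of their own. Each candidate is tested by Kruskal–Wallis at 0.05 with Hochberg adjustment.

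*Setting A.* 15 candidates, 8 of them mobility measures; true log-odds 0.9 per SD; smaller class about 20% or 50%; N = 160 or 200; 300 runs each. Mean number flagged of 7 redundant measures:

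| ρ | Separate tests, Hochberg | Separate tests, Benjamini–Hochberg |
|---|---|---|
| 0.5 | 1.4–3.1 | 2.4–4.5 |
| 0.7 | 3.5–5.6 | 4.9–6.4 |
| 0.9 | 6.0–6.9 | 6.5–7.0 |

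A joint logistic model at unadjusted 0.05 flags 0.3–0.5 of 7 in all these settings, close to the chance rate of 7 × 0.05 = 0.35. The Benjamini–Hochberg column is shown because the plan speaks of false discovery rates; that reading lengthens the list.

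*Setting B.* 20 candidates, 10 of them mobility measures; one further independent true predictor of equal strength; at-risk class about 30%; 200 runs each. Mean number flagged of 9 redundant measures at ρ = 0.5 / 0.7 / 0.8:

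| Log-odds per SD | N = 160 | N = 200 |
|---|---|---|
| 0.4 | 0.3 / 0.6 / 0.8 | 0.3 / 0.9 / 1.0 |
| 0.6 | 0.5 / 1.8 / 2.5 | 0.9 / 2.3 / 3.7 |
| 0.8 | 1.2 / 3.1 / 4.9 | 1.6 / 4.7 / 6.6 |

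At log-odds 0.4 the true mobility predictor is itself found in only 14–26% of datasets.

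*Setting C.* As B, but the mobility predictor has log-odds 0.8 and the independent one 0.5; 400 runs each. At ρ = 0.3 / 0.5 / 0.7 / 0.8 the redundant flags of 9 are 0.2 / 1.4 / 3.7 / 5.2 (N = 160) and 0.4 / 1.8 / 4.6 / 6.6 (N = 200). The independent true predictor is flagged in 27–45% of runs. At ρ = 0.7 and N = 160 an average redundant measure is flagged in 3.7/9 = 41% of runs, so a list can be padded and incomplete at once.

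**4. How large a joint model the data can carry.** With 15 parameters and 160 patients, the smaller class supplies 160 × 0.50/15 = 5.3 patients per parameter if it holds half the sample, 160 × 0.20/15 = 2.1 at 20%, and 160 × 0.05/15 = 0.5 at the 5% minimum the plan allows. An unpenalised model over all candidates would not be reliable in the last two cases.

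**The case against.** The best defence is that this is a condensed article. The list of tests is introduced as an example, a full analysis plan may exist, and details such as the penalty, optimism correction and calibration are usually left to it. That holds for the details. It does not remove the mismatch: the article states a method and a multiplicity rule for this hypothesis, and that kind of method cannot answer the stated aim. Elsewhere the article is specific, naming fit criteria, an entropy threshold and a proportional-hazards check.

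Four stronger readings are tempting and are not supported.
- A reader might infer that Aim 3 has no multivariable analysis at all. The Cox models under Hypothesis 1.2 bear on its falls part. They are exploratory, concern time to first fall rather than class, and name no candidates, selection rule or performance measure. The confounder and parsimony sentences do not supply these either.
- A reader might infer that every measure correlated with a true predictor will be flagged. The simulations show otherwise: at ρ = 0.5 it is a minority, and with weak effects low power is the main problem.
- A reader might take strong overlap among the clinic mobility tests as given. The documents report no correlations.
- A reader might treat the Discussion's remark on predictive power as a pre-specified test of added value. It is a stated intention that appears in neither the aims nor the analysis section.

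**Conclusion.** The concern holds for Hypothesis 2.1 and class membership. The stated tests cannot identify a smallest joint set, cannot show redundancy, and give no measure of prediction, so the Discussion's intention on predictive power is not met either. This conclusion follows from the text and needs no simulation.

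The practical size is uncertain. Under the assumptions above, the mean number of redundant measures flagged runs from 0.2 of 9 (ρ = 0.3) to 6.9 of 7 (log-odds 0.9, ρ = 0.9, N = 200). With weak effects the list is short and real predictors are often absent from it. All settings assume a single true mobility predictor with equal correlations among the mobility measures, which is a simplification.

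**What to change.** Make the primary Hypothesis 2.1 analysis a pre-specified multivariable model of class membership (logistic or multinomial):
- Use shrinkage or penalised selection, for example lasso or elastic net, over a named list of baseline and treatment candidates. The choice among such methods matters less than fixing it in advance.
- Limit the number of candidates by the size of the smallest class. At the 5% minimum this is 8 patients of 160 or 10 of 200, which supports very little.
- Report optimism-corrected discrimination and calibration.
- Compare nested models with and without the simple mobility tests, judged on corrected performance.
- Exclude as predictors any measures used to build the classes, or report them separately. The classes come from intercepts and slopes of functioning measures, and the six in the most complex model are not named. A mobility test among them would be predicting a class it helped to define, and correcting the regression alone would not remove that inflation.
- Keep the one-variable tests as description.

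The cost is wording and some programming, with no new data. Corrected performance will look less favourable, and few predictors can be supported if a class is small.

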### Sample size/power calculation

Although simulation methods are available to help estimate sample size for

GMM, this requires known values for all model parameters and is not defensible given the unknowns in this domain. With 2 symptom measures (severity and interference) and 6 function measures in our most complex GMM model, however, our n-to-items ratio meets conservative sample size recommendations for related approaches (20:1) [60] and would require 160 complete cases. To maximize statistical power we will fit parsimonious models after extensive preliminary associative analyses. Regarding class comparisons, assuming 80% power, two-sided α of 0.05, and 2 equal groups, we will be able to detect small-medium sized differences in fall rates and other continuous variables between groups (Cohen’s *d* = 0.40). For categorical variables, we will be able to detect small-medium effects (w = 0.25) for cross-tabulation tables with as many as 4 degrees of freedom. Evaluable data on 200 participants is a feasible number and will allow us to address each aim while accounting for up to ~ 20% attrition.

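### Kendall's tau-b, one of two example tests for predictors of latent class, depends on arbitrary class numbering once there are three or more classes

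*Protocol article*

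**What the plan says.** Under Hypothesis 2.1 in the protocol article's Specific analysis plan, the tests concern "the association between latent class membership and sociodemographic, clinical, and mobility measures depending on level of scale (e.g., Kendall/s tau-b". Read to the end of the list of examples, the choice of test is made "depending on level of scale (e.g., Kendall/s tau-b or Kruskal–Wallis tests". So one variable in every such test is class membership, and tau-b and Kruskal–Wallis are examples, not a closed list.

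Class membership is built under Hypothesis 1.2. Individual intercepts and growth estimates for each measure enter a mixture model "to identify patient clusters with distinct symptom and function trajectory profiles", and then "the highest membership probability will be used to make a final class assignment". No step ranks the classes.

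The number of classes is open. The Specific analysis plan expects that "At least two classes of patients with distinct trajectories of change in symptoms and functioning can be identified", and Study aims and hypotheses says "we can identify 2 or more distinct trajectories of CIPN and physical functioning associated with falls". Models with k and k-1 classes are compared without an upper limit, apart from a floor of 5% of the sample per class.

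**The concern.** Tau-b counts concordant and discordant pairs, so it needs an order on both variables. Choosing by level of scale can settle how a predictor is measured, but it does not give the classes an order. Numbers attached to mixture classes are labels. Classes defined by starting level and change on several symptom and function measures need not fall on one scale: one class may start poorly and stay stable while another starts well and declines.

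With three or more classes, tau-b therefore tests for a trend across the label order, whereas the stated question is whether the predictor is associated with class at all. An ordinal predictor could be kept or dropped because of how the software numbered the classes. The planned multiplicity adjustment cannot repair this, because it works on p-values that already depend on the labels.

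**Working it through.** **Plan's own figure.** For categorical variables the Sample size section states w = 0.25 with up to 4 degrees of freedom at 80% power and two-sided 0.05. The noncentrality is N × w² = 200 × 0.0625 = 12.5, which gives power 0.82 for the chi-square test. The figure reproduces at N = 200 and is not in dispute. It is used here only to set an effect of realistic size.

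**Two classes.** Swapping the labels only flips the sign of tau-b. In a test data set with two groups of 100, both labellings gave p = 0.220, the same as the Mann–Whitney test without continuity correction. There is no defect.

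**Three classes: inputs.** n = 160 is the number of complete cases in the Sample size section. The article gives no class sizes or predictor effects, so the following are assumptions: three equal classes A, B, C and a three-level ordinal predictor with probabilities

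- A: 0.42, 0.35, 0.23
- B: 0.35, 0.36, 0.29
- C: 0.19, 0.33, 0.48

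The average distribution is 0.320, 0.347, 0.333. Summing (p − average)²/average within each class gives 0.0633, 0.0090 and 0.1181. Their mean is 0.0635, so w = √0.0635 = 0.252.

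**Why numbering matters.** For two classes let δ = P(higher value in the second) − P(lower value in the second).

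- A to B: 0.3745 − 0.2858 = 0.0887
- A to C: 0.5082 − 0.1861 = 0.3221
- B to C: 0.4563 − 0.2192 = 0.2371

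With equal classes, the expected numerator of tau-b is proportional to the sum of the three δ, each signed by the label order. The denominator depends only on ties and does not change with numbering.

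- Order A, B, C: 0.0887 + 0.3221 + 0.2371 = 0.648
- Order B, A, C: −0.0887 + 0.3221 + 0.2371 = 0.471
- Order A, C, B: 0.0887 + 0.3221 − 0.2371 = 0.174

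The other three numberings are mirror images with the same p-values. The data are identical throughout, yet the signal falls to 0.174/0.648 = 27% of its largest value.

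**Simulated power, two-sided 0.05, n = 160:**

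| | Shorter runs | Runs of 6,000 data sets |
|---|---|---|
| Kruskal–Wallis | 0.83–0.85 | 0.82–0.83 |
| Chi-square | 0.72–0.76 | 0.72–0.74 |
| Tau-b, A B C | 0.87–0.89 | 0.87–0.88 |
| Tau-b, B A C | 0.56–0.59 | 0.59–0.61 |
| Tau-b, A C B | 0.16 | 0.13–0.14 |

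The columns differ by a few points, mostly simulation error: with 1,000 data sets the standard error is √(0.15 × 0.85/1000) = 0.011 near 0.15 and about 0.016 near 0.6.

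**Other assumed settings.** With classes of 50%, 30% and 20%, n = 160 and w = 0.25, Kruskal–Wallis has 0.79 and tau-b 0.80, 0.35 or 0.32. With a stronger three-level predictor and n = 200, Kruskal–Wallis has 0.96, chi-square 0.91 and tau-b 0.98, 0.57 or 0.41.

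**The case against.** The strongest reply is that the article does not commit to tau-b on unordered classes. It gives a selection rule with two examples; applied strictly, the rule would admit tau-b only when both variables are at least ordinal. Kruskal–Wallis, the main remedy, is the other example. A condensed article may also leave the pairing of tests and variables to a fuller plan. This stands as a limit on severity. It does not remove the point, because tau-b is named for tests in which one variable is always class membership, and no ordering is stated.

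It is also fair that two classes may emerge: the power statement assumes two equal groups, and 4 degrees of freedom fits a 2 × 5 table as well as a 3 × 3 one. The investigators may order classes by severity, since they expect symptoms and functioning to worsen together and will describe the classes first. In that case, with a monotone predictor, tau-b is slightly the better test.

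Three stronger readings are tempting and are not supported.

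- A reader might infer that the stated detectable effect is wrong for the named test. The article gives "small-medium effects (w = 0.25) for cross-tabulation tables with as many as 4 degrees of freedom" for categorical variables and does not offer it for tau-b. If anything, it suggests that nominal cross-tabulation tests are already intended.
- A reader might infer that all predictor screening is affected. Many listed predictors are continuous or counts (age, body mass index, cycles, cumulative dose, gait and balance), for which Kruskal–Wallis is the natural choice, and some are nominal (sex, type of chemotherapy). The exposure is mainly ordinal predictors.
- A reader might infer false positives. If a predictor is unrelated to class, tau-b keeps its error rate under any numbering fixed without reference to that predictor.

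**Conclusion.** The point holds in a limited form. Tau-b, as one of two example tests, does not suit a nominal class variable when there are three or more classes, and nothing in the article restricts it to two classes or to ordered ones. The dependence on labels is a mathematical property and needs no assumption. Its size does: the power range of about 0.16 to 0.89 (down to about 0.13 in the longer runs), against 0.82 to 0.85 for Kruskal–Wallis, rests on three equal classes, one assumed three-level predictor and 160 complete cases. The loss arises only under numberings that break the predictor's order across classes. Severity is minor; it is a cheap improvement.

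**What to change.** In the paragraph under Hypothesis 2.1, state that tau-b will be used only when two classes are retained, or when the classes have been placed in a clinical order fixed before any predictor is examined. In all other cases treat class as nominal: the already named Kruskal–Wallis test for ordinal and continuous predictors, and chi-square or Fisher's exact test for categorical ones.

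The cost is a wording change. No data collection or sample size is affected. The downside is a few points less power than tau-b when the numbering happens to match a true monotone order: 0.872 − 0.828 = 0.044 with equal classes and 0.804 − 0.789 = 0.015 with 50/30/20% classes. Where such an order is expected on clinical grounds, fixing it in advance keeps that gain.
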